### Outcome measures

**Primary outcomes**

1.
**Foot Function Index (FFI)**
the Foot Function Index (FFI) was designed to analyze the effect of foot abnormalities on performance in terms of pain, functional limitations, and activity restriction. The internal consistency was between 0.96 and 0.7.
^
15
^
2.
**The Modified Star Excursion Balance Test (mSEBT)**
The SEBT (Star Excursion Balance Test) is a multi-dimensional test that includes power, mobility, and postural control. This is a dynamic balancing measurement that poses a substantial challenge to players and healthy and active adults. The evaluation is used to measure functional ability as well as to screen for inadequacies in dynamic balance caused by musculoskeletal disorder. coefficients of variation ranging from 2.0 to 2.9 percent, the mSEBT has been shown to be a valid indicator of dynamic balance.
^
17
^

**Secondary outcome**

1)
**The Visual Analogue Scale (VAS)**
To determine the intensity of the pain this scale is used. The VAS is a 10 cm line that has two terminals marked with the numbers 0 (“no discomfort”) and 10 (“pain as horrific as it can be”). Ask the patient to rate their current level of discomfort and mark the line accordingly. Using a ruler determine the distance in centimetres between baseline and the current pain mark.
^
18
^
2)
**Weight Bearing Lunge Test (WBLT)**
Ankle dorsiflexion range is determined with this procedure. In this test with the help of inch tape distance will be measured. Inter-rater ICC values for angles were 0.97 and 0.99. The analysis shows evaluating a dorsiflexion range with this method have great reliability.
^
19
^

### Sample size calculation

Sample size calculation resulted at 5% level of significance considering Z (1-α) value = 1.96 and (1- β) at power of 80% = 0.84 measuring the expected mean difference for superiority (effect side) of (δ) = 2.602 and standard deviation (σ) = 3.24

Formula Using Mean difference

$$n1=n2=2\frac{{\left(Z_{\alpha }+Z_{\beta }\right)}^{2}\sigma^{2}}{{\left(\delta \right)}^{2}}$$

Primary variable – (Foot Functional Index)

Mean. (Pre) result on Foot Functional Index for foot core exercises with conventional physiotherapy = 72.68

Mean. (Post)- result on Foot Functional Index for foot core exercises with conventional physiotherapy = 59.67 ± 10.69

Difference (mean ± SD) = 13.01 ± 3.24 (As per reference article)

Clinically relevant superiority = 20% = (13.01 *20)/100 = 2.602

$$\text{N1}=2^{*}\left[{\left(1.96+0.84\right)}^{2}\;{\left(3.24\right)}^{2}\right]/{\left(2.602\right)}^{2}=25$$

Minimum samples required = 25 per group

Considering 30% drop out = 8

Total sample size required = 33 per group

Assumptions

$$Z_{\alpha }=1.96$$

α=TypeIerrorat5%

$$Z_{\beta }=0.84\;\left(1-\beta \right)=\text{Power}\;\mathrm{at}\;80\%$$

σ=std.dev

Ref Article: - Jadhav and Gurudut.
^
20
^

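### The 80% power claim rests on a change SD of 3.24 which, beside the printed post-treatment SD of 10.69, needs an unexplained pre-post correlation of at least 0.953

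*Protocol article*

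**What the plan says.** The section on sample size calculation names the FFI as the variable that drives the sample size. It takes its inputs from one reference article, for patients given foot core exercises with conventional physiotherapy:

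- Baseline: "Mean. (Pre) result on Foot Functional Index for foot core exercises with conventional physiotherapy = 72.68". No SD is printed.
- After treatment: "Mean. (Post)- result on Foot Functional Index for foot core exercises with conventional physiotherapy = 59.67 ± 10.69".
- Change: "Difference (mean ± SD) = 13.01 ± 3.24 (As per reference article".
- Target difference: "Clinically relevant superiority = 20% = (13.01 *20)/100 = 2.602".
- Error rates: "5% level of significance considering Z (1-α) value = 1.96" and "1- β) at power of 80% = 0.84".

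The usual two-sample formula is applied with σ = 3.24 and δ = 2.602. The result is "Minimum samples required = 25 per group", raised to 33 for dropout. The sections on analysis and on the primary outcome plan to compare the groups on mean change from baseline to six weeks, with an unpaired t-test if the data are normal. The SD of individual change is therefore the right kind of quantity for σ.

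**The concern.** The SD of change and the SD at one visit are linked through the pre-post correlation. A change SD less than a third of the post-treatment SD (3.24/10.69 = 0.30) is possible only if patients keep almost exactly their relative position from baseline to six weeks. Nothing in the article shows that they do.

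σ enters the formula squared, and this is the article's only justification of the sample size. If the change SD is nearer to what 10.69 suggests at a lower correlation, a trial described as a superiority trial would have little chance of detecting the difference it calls clinically relevant. A non-significant result could then be taken as a sign that the two programmes work alike.

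**Working it through.** **Inputs.** From the section on sample size calculation: post-treatment SD 10.69; change SD 3.24; δ = 2.602; Z values 1.96 and 0.84; 25 evaluable and 33 enrolled per group. The baseline SD and the pre-post correlation r are not printed, so values used for them are assumptions.

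**1. The plan's own figures.**
- Mean change: 72.68 − 59.67 = 13.01, and 20% of it is 2.602.
- n = 2 × (1.96 + 0.84)² × 3.24² / 2.602² = 24.3, rounded up to 25.
- Power at 25 per group with σ = 3.24 is 81.0% by the normal approximation and 79.5% by the noncentral t.

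The arithmetic reproduces.

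**2. The correlation that the two SDs imply.** With B the baseline SD:

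3.24² = B² + 10.69² − 2 × r × B × 10.69, so r = (B² + 10.69² − 3.24²) / (2 × B × 10.69).

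- This is smallest at B = √(10.69² − 3.24²) = 10.19, where r = √(1 − (3.24/10.69)²) = 0.953.
- With equal SDs, r = 1 − 3.24²/(2 × 10.69²) = 0.954.
- The SD of a difference cannot be less than the gap between the two SDs. So 3.24 is possible only if B lies between 10.69 − 3.24 = 7.45 and 10.69 + 3.24 = 13.93.

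**3. Power at other correlations, assuming B = 10.69.**
- Change SD = 10.69 × √(2(1 − r)).
- Power is for δ = 2.602, two-sided 5%, noncentral t.
- n = 2 × 2.80² × SD² / 2.602², rounded up.
- Detectable difference at 80% power with 25 per group = 2.80 × SD × √(2/25).

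| r | Change SD | Power, 25 per group | Power, 33 per group (no dropout) | n per group for 80% | Detectable difference, 25 per group |
|---|---|---|---|---|---|
| 0.5 | 10.69 | 13% | 16% | 265 | 8.5 |
| 0.7 | 8.28 | 19% | 24% | 159 | 6.6 |
| 0.8 | 6.76 | 27% | 34% | 106 | 5.4 |
| 0.9 | 4.78 | 47% | 59% | 53 | 3.8 |

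At r = 0.95 the change SD is 3.38 and power at 25 per group is 76%. The claim therefore nearly holds at that extreme and falls quickly below it.

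**4. Sensitivity to the assumed baseline SD.** Near the two ends of the feasible range, power at 25 per group (normal approximation) is:

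| Baseline SD | r = 0.5 | r = 0.7 | r = 0.8 | r = 0.9 |
|---|---|---|---|---|
| 7.5 | 16% | 23% | 29% | 44% |
| 13.9 | 11% | 15% | 20% | 31% |

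For a given r, the smallest change SD that any baseline SD allows is 10.69 × √(1 − r²). At r = 0.9 that is 4.66, and power is about 51% (normal approximation). The same SD applies to an analysis adjusted for baseline, so adjustment does not restore 80% either.

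**The case against.** The strongest reply is that nothing has been shown to be wrong. The two figures describe different quantities, the article labels 3.24 as an SD of the difference, and a change SD is what the planned comparison needs. The two can coexist if r is at least 0.953. All of this stands. It means that σ is unsupported; it does not mean that σ is impossible. The power figures also depend on a baseline SD and correlations that the article does not give, which also stands, and that is why they are shown as a range.

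Four stronger readings are tempting, and the document does not support them:

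- *That 3.24 is a standard error or a transcription error.* Only the reference article could settle this, and it is not at hand.
- *That the FFI's reliability rules out 0.953.* The outcome section says "The internal consistency was between 0.96 and 0.7". Internal consistency is not a strict ceiling on a pre-post correlation, the article does not say whether the range refers to subscales or the total score, and its upper end exceeds 0.953.
- *That the standardised effect shrinks from 2.602/3.24 to 2.602/10.69.* This compares a change scale with a single-visit scale. The second ratio applies to the analysed change only if r = 0.5 with equal SDs.
- *That the investigators intend to read a null result as equivalence.* The article calls the trial a superiority trial and already plans an effect size with a 95% CI. The risk of misreading follows from low power; it is not stated intent.

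**Conclusion.** The concern holds as a matter of an unsupported input. The stated 80% power for 2.602 FFI points depends on a pre-post correlation of at least 0.953, which the article neither states nor justifies. This bound rests only on the two printed SDs and needs no assumption about baseline.

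The size of the shortfall does rest on assumptions. With a baseline SD of 10.69 and r from 0.5 to 0.9, power at the planned 25 evaluable per group is 13% to 47%. With all 33 per group retained it is 16% to 59%. At r = 0.9 and 25 per group, no choice of baseline SD lifts power above about 51%. If the reference article confirms 3.24 as the between-patient SD of change, the calculation has its source and only the explanation is missing. Until then, the 80% figure should not stand as written.

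**What to change.** Keep N = 66 and revise the sample size section:

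1. Verify in the reference article what 3.24 is, and say so. Give the baseline SD and the correlation that it implies.
2. Unless 3.24 is confirmed as a between-patient SD of change, withdraw the claim of 80% power for 2.602 points. Report instead the power, or the detectable difference, at 25 per group over a stated correlation range. For r = 0.5 to 0.9 with equal SDs, the detectable difference runs from about 8.5 down to 3.8 points.
3. State that the 95% CI already planned for the difference in mean change will be interpreted against 2.602, so that a non-significant result is not taken to show similarity.

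The cost is one check of a source, some rewording and a less favourable stated power. No extra patients are needed. The article says that the study has not yet started, so the change can be made before recruitment.

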## Abstract

Plantar fasciitis is generally described as an inflammation of the plantar fascia and adjacent tissues around calcaneus tuberosity. Plantar fasciitis onset has been proposed to have an internal mechanical cause, even though this is inadequately recognized. Studies related to alternation in lower-extremity biomechanics that leads to reduced domes of the foot are hypothesized to cause tension in the underlying fascia. Similarly, despite a wealth of anecdotal data suggesting a direct connection between foot mechanism and disability. This condition typically leads to calf muscular stiffness, soreness in the bottom of the feet, decreased range and foot function, strength, and balance impairment. These results in interference with the normal biomechanics of ambulation. A total of (n=66) individuals with plantar fasciitis will be selected for the trial. Subjects will be allocated to Groups A and B at equal allocation with randomization. Group A will undergo foot core exercises, while Group B will undergo ankle proprioceptive neuromuscular facilitation, with both groups receiving conventional treatment. The regimen lasts for 40 minutes, 5 days, for 6 weeks. The outcome measures will be assessed on Foot Functional Index, modified Star Excursion Balance Test (mSEBT), Visual Analogue Scale (VAS), and Weight Bearing Lunge Test (WBLT) be assessed at the initiation and completion of the entire treatment protocol. Prior and after therapeutic intervention results will be analyzed. Based on the comparison of the two treatments' effects on measuring outcomes in individuals with plantar fasciitis, an analysis will be conducted.

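### The 30% drop-out allowance is added to the required number instead of divided out, so 33 per group leaves about 23 completers, not the stated minimum of 25

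*Protocol article*

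**What the plan says.** The Sample size calculation section of the protocol article sizes the trial on the Foot Function Index with the usual two-sample formula for means. Its inputs are a 5% significance level with z = 1.96, 80% power with z = 0.84, a difference set by "Clinically relevant superiority = 20% = (13.01 *20)/100 = 2.602", and "standard deviation (σ) = 3.24".

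Three lines then give the result: "Minimum samples required = 25 per group", "Considering 30% drop out = 8" and "Total sample size required = 33 per group".

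The Protocol section repeats 33 per group, and the Abstract gives 66 in total with equal allocation. Nothing in the article defines the 30% as anything other than a drop-out proportion.

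**The concern.** A drop-out rate is a share of those enrolled, because they are the ones who can leave. The plan applies it to the number it wants to have at the end. That always gives too small an enrolment figure, and the gap widens as the rate rises; at 30% it is no longer a rounding matter.

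At stake are two of the plan's own statements. If the allowed drop-out occurs, the trial falls below the number it calls the minimum required and below its stated power. This holds even if the difference and the SD are accepted as they stand.

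**Working it through.** **Inputs** (all from the Sample size calculation section, except the 1:1 allocation, which is in the Abstract): z = 1.96 and 0.84; δ = 2.602; σ = 3.24; drop-out 30%; minimum 25 and enrolled 33 per group.

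**1. Reproduce the plan's figures.**

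n = 2 × (1.96 + 0.84)² × 3.24² / 2.602² = 24.31, rounded up to 25. This agrees with the plan.

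0.30 × 25 = 7.5, rounded up to 8; 25 + 8 = 33. This also agrees, so 33 comes from adding 30% of the required number.

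**2. Apply the stated drop-out to the stated enrolment.**

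33 × (1 − 0.30) = 23.1, so about 23 completers per group. This is below 25, and also below the unrounded 24.31.

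**3. Drop-out that 33 per group can absorb.**

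1 − 25/33 = 8/33 = 24.2%.

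**4. Enrolment needed to keep 25 after a 30% loss.**

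25 / (1 − 0.30) = 35.7, so 36 per group, 72 in total (check: 36 × 0.70 = 25.2). Starting from the unrounded figure, 24.31 / 0.70 = 34.7, so 35, which is still above 33.

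**5. Power with the plan's δ and σ.**

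Normal formula: power = Φ(δ / (σ√(2/n)) − 1.96). At n = 23 this is Φ(2.602 / (3.24 × √(2/23)) − 1.96) = Φ(0.763) = 0.777. The t-test column uses the noncentral t distribution with 2n − 2 degrees of freedom.

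| Completers per group | Normal formula | Unpaired t-test |
|---|---|---|
| 25 (plan's minimum) | 81.0% | 79.5% |
| 23 (33 enrolled, 30% lost) | 77.7% | 75.9% |

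On a like-for-like basis the missing two completers cost 3.3 points (normal) or 3.5 points (t-test, from the unrounded values).

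**The case against.** The best argument on the other side is that this is minor. The plan rounds 24.31 up to 25, so measured against the exact requirement the gap is about 1.2 completers per group (24.31 − 23.1). On the plan's own formula, power falls only 2.3 points below 80%. That stands: the practical effect is small.

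A second point is that setting the t-test's 75.9% against a target of 80% mixes two methods. The plan's 80% comes from the normal formula, and by the t-test even a full 25 per group gives 79.5%. That also stands. The like-for-like loss is 81.0% to 77.7%, or 79.5% to 75.9%. Both bases are worth showing, because the Analysis section names the unpaired t-test for the between-group comparison.

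Third, the 30% is a planning allowance and not a forecast, and the shortfall appears only if losses exceed 24.2%. This is a fair caution on wording, but an allowance is meant to protect the required number at the rate named, and this one does not.

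Two further defences fail. Adding the percentage is a familiar shortcut, but 33 × 0.70 is still not 25. Nor does the random-effects model described under Primary outcome restore the number: outcomes are measured only at baseline and six weeks, so a patient without the six-week value has no observed change and adds almost nothing to the comparison.

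**Conclusion.** The concern holds. A minimum of 25, a 30% drop-out and an enrolment of 33 per group are mutually inconsistent. At 30% loss about 23 per group remain, two below the minimum, and power is 77.7% (normal formula) or 75.9% (t-test) against the stated 80%. Thirty-three per group covers a loss of up to 24.2%.

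The power figures take δ = 2.602 and σ = 3.24 as given and pass no judgement on either; they show an internal inconsistency, not the trial's true power. The completer counts need no such assumption. The consequence is modest, but the wrong step is in the calculation that justifies the enrolment figure.

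**What to change.** Enrolment can stay at 33 per group if the drop-out statement is corrected in one of two ways:

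- State that 33 per group keeps 25 completers for drop-out of up to 24%. This lowers the planned allowance from 30%, so the sponsor should say why the lower rate is reasonable; otherwise the rate has merely been fitted to the number already chosen.
- Keep 30% and state that about 23 per group would then remain, with power of about 78% on the plan's formula or about 76% by the unpaired t-test, naming the basis used.

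Either costs one sentence with a slightly less favourable figure, and no patients.

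If the sponsor wants to keep both the 30% allowance and the minimum of 25, the enrolment figure becomes 36 per group and 72 in total: 3 more per group, 6 overall. The Abstract and the Protocol section would then need the same change. The article says the study has not yet started, so any of these can be made before enrolment.

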### Analysis

All the results will be calculated using SPSS 27 version. Demographic variables (Confounding factors) as per quantitative assessment will be resulted for finding observational values on mean Standard deviation minimum and maximum. Quantitative assessment will be observed on frequency and percentage. The data for inferential statistics, with outcome variables will be tested for normality using Kolmogorov Smirnov Test. A parametric test will be used if the data follows normal distribution. Non-normal data will be attempted for transformation to normality by using mathematical algorithm such as log or exponential function or box cox method. For finding the significance over the mean pre- and post T-paired will be used for analysis if data still persist with non-normal distribution alternative Wilcoxon test will be used for finding the difference for mean significance between the two groups (Inter) un-paired t-test will be used while the Man-Whitney will be used as an alternative t-test for non-normal data Association and analysis for finding the significance of confounding parameters will be evaluated using Chi square test or Fischer Exact Test or using multi-variant analysis.

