### Primary endpoint

To predict the difference in effect size between the active and control groups, secondary outcomes (the visual analogue scale and the weight bearing lunge test) will be examined in accordance with the mixed model effect. If the data is distributed normally, the T-test (unpaired) will be performed to determine whether there is a significant difference between the means of the two groups. The data will be transformed into a normal distribution for non-normal distributions using mathematical techniques. If the primary variable's data still exhibits a non-normal distribution, an alternative non-parametric test will be used (Chi square, Mann Whitney, Wilcoxon test).

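### A normality test on the outcome data can move the primary comparison off the FFI-point scale on which the trial is sized and reported, and no rule says whether this sequence or the mixed model takes precedence

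*Protocol article*

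**What the plan says.** The protocol describes the primary comparison in three places.

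- **Analysis.** Outcome variables are "tested for normality using Kolmogorov Smirnov Test. A parametric test will be used if the data follows normal distribution". If they fail, "Non-normal data will be attempted for transformation to normality by using mathematical algorithm such as log or exponential function or box cox method". If that does not work, Wilcoxon replaces the paired pre-post t-test and Mann-Whitney replaces the unpaired t-test between groups. In this section chi-square and Fisher's exact test serve only for associations with confounders.
- **Primary outcome.** FFI and mSEBT are compared on mean change from baseline to six weeks. The model has random participant effects and fixed effects for group and visit. An effect size for the difference in mean change is to be given with its 95% CI. No normality condition is attached.
- **Primary endpoint.** After a sentence on the secondary outcomes, the sequence of t-test, transformation and fallback appears again. For a primary variable that is still non-normal, "an alternative non-parametric test will be used (Chi square, Mann Whitney, Wilcoxon test" is the last step.

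The Sample size calculation is written in raw FFI points: "Difference (mean ± SD) = 13.01 ± 3.24 (As per reference article" and "Clinically relevant superiority = 20% = (13.01 *20)/100 = 2.602".

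**The concern.** The outcome data choose the method, and the methods do not estimate the same thing. An unpaired t-test on change estimates a difference in FFI points. A t-test after a log, exponential or Box-Cox transformation estimates a difference on another scale, and no back-transformation is given. Mann-Whitney addresses the ordering of the two distributions. Chi-square compares proportions, so a continuous score would need a cut-point, and none is given. As the Analysis section reads, Wilcoxon is the paired pre-post test, which does not compare groups.

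The trial could therefore end with a primary result that cannot be set against 2.602 points and does not supply the promised interval for the difference in mean change. The mixed model would supply that interval, but the protocol does not say that it overrides the sequence. With two accounts of the primary analysis and no order between them, the choice would be made after the data are seen.

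**Working it through.** **1. The plan's own figure.** Inputs from the Sample size calculation: z = 1.96 and 0.84, σ = 3.24, δ = 0.20 × 13.01 = 2.602, equal groups.

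n = 2 × (1.96 + 0.84)² × 3.24² / 2.602² = 2 × 7.84 × 10.4976 / 6.7704 = 24.31, rounded up to 25 per group. This reproduces the stated figure. The formula concerns a difference of raw-scale means, and no normality switch enters it. On these inputs a two-sided raw-scale comparison has 81.0% power at 25 per group and 90.4% at 33. Fixing such a comparison in advance leaves the stated size unchanged.

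**2. What each permitted route estimates.**

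| Route | Quantity | Readable against 2.602 points? |
|---|---|---|
| Unpaired t-test on raw change | Difference in mean change, FFI points | Yes |
| Mixed model (Primary outcome section) | Difference in mean change, FFI points | Yes |
| t-test after log, exponential or Box-Cox | Difference on the transformed scale | No |
| Mann-Whitney | Ordering of the two distributions | No |
| Wilcoxon (paired, as in Analysis) | Within-group pre-post shift | No |
| Chi-square | Proportions either side of an unstated cut-point | No |

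**3. How often the sequence would leave the raw scale.** The documents give no distribution shape, so this is an illustration under assumptions. Change scores had mean 13.01 and SD 3.24, either normal or gamma-shaped with skewness 1 or 1.4. The sequence was a Lilliefors-type Kolmogorov-Smirnov test in each arm at 5%, then log (shifted if any value was not positive), then Mann-Whitney. There were 1,500 trials per scenario, at 25 and 33 per group, with a between-group shift of 0 or 2.602.

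| Assumed shape | Leaves raw t-test | Ends on log scale | Ends on Mann-Whitney |
|---|---|---|---|
| Normal | 8-10% | about 3% | 6-8% |
| Skewness 1 | 38-48% | 27-37% | 10-14% |
| Skewness 1.4 | 63-75% | 32-42% | 28-34% |

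Type I error of the whole sequence was 4.7-6.2%, with a Monte Carlo standard error of √(0.05 × 0.95 / 1500), about 0.6 percentage points. Power was similar to or higher than that of the plain t-test. Free choice among several transformations was not simulated.

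**4. When log or Box-Cox would be undefined.** Both need positive values. The protocol does not say whether scores or changes would be transformed. Raw FFI means are 72.68 and 59.67, so raw scores would rarely be a problem. If changes are transformed, and assuming they are normal, the share at or below zero is Φ(−13.01 / SD):

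- SD 3.24, the stated change SD: Φ(−4.02), about 0.003%.
- SD 10.69: Φ(−1.22), about 11%, or 0.11 × 66 ≈ 7 patients.

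The protocol attaches 10.69 to the post-treatment score. Using it for change is an assumption: with equal pre and post SDs, 10.69 × √(2(1 − r)) equals 10.69 when r = 0.5.

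**The case against.** **The Primary outcome section already gives an ungated raw-scale analysis.** This is correct, and it means that the normality sequence is not the only stated route to the primary result. But the Primary endpoint section applies the sequence to the primary variable by name, and neither section yields to the other. The fair description is two unreconciled primary analyses.

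**A condensed article may leave detail to an analysis plan.** This stands for the level of the normality test, the order of transformations and any residual checks, and their absence is not held against the protocol. The routing rule and its end points, however, are written here.

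**Chi-square is probably loose wording.** Possibly so, since the Analysis section names Mann-Whitney as the between-group alternative. The parenthesis still lists chi-square for the primary variable and should be corrected. Wilcoxon might also be meant as the rank-sum test, but the Analysis section uses it for the paired comparison.

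**Two stronger readings are tempting.** A reader might infer that the preliminary test inflates the type I error. The simulation does not show this for the one fixed path examined, and analyst choice among transformations was not tested. A reader might also infer that log or Box-Cox would fail for a sizeable share of patients. The documents do not support that: it could arise only if changes are transformed, and on the stated change SD almost nobody is affected.

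**Conclusion.** The concern holds for scale and estimand. As written, a test on the outcome data can move the primary comparison from a difference in FFI points to a quantity that answers neither the Sample size calculation nor the promised confidence interval, and no precedence rule prevents it. The same sequence covers mSEBT, the other primary outcome.

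How often this would happen depends on a shape that the documents do not give. Under the assumptions used, it ranges from about 8-10% of trials (normal data) to 63-75% (skewness 1.4). Inflation of the type I error has not been demonstrated. The undefined-transformation issue is conditional, with a share from about 0.003% to about 11%, the upper figure resting on an assumed change SD.

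The change should be made. The protocol reports that the study has not started, so the rule can still be fixed before any outcome data exist.

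**What to change.** - State one primary estimate for FFI, and likewise for mSEBT: the between-group difference in mean change to six weeks on the original scale, with 95% CI, whatever a normality test shows. It can come from the model in the Primary outcome section or from a linear model adjusted for the baseline value, which is already collected. Name one of the two.
- Remove the Kolmogorov-Smirnov gate and the transformations as determinants of the primary test.
- Remove chi-square for continuous outcomes, and state that Wilcoxon applies only to paired pre-post comparisons.
- Keep Mann-Whitney, or bootstrap or robust confidence intervals, as named sensitivity analyses.
- Bring the Analysis, Primary outcome and Primary endpoint sections into line, and treat VAS and WBLT in the same way.

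The cost is protocol wording. The stated 25 per group does not change. The downside is a slight loss of efficiency if an outcome is very skewed.
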